**Discussion:**

The discussion will take into account the limitations of the study, together with considerations such as the choice of a simple, safe method to treat this shoulder complaint, the choice of the control group, and the blinding of the patients, evaluators and those responsible for carrying out the final analysis.

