### Study subjects

Patients referred to the Rehabilitation services of the health centres participating in the study. These centres are part of the public health systems of the regions of Andalusia and Murcia (Spain). The patients presented chronic symptoms of subacromial syndrome (rotator cuff tendinitis and subacromial bursitis) and were offered treatment with physiotherapy together with acupuncture or transcutaneous stimulus. They were informed of the characteristics of the study and of the techniques to be used, as well as of the possible risks (infection, lipothymia, hematomas). They were told they could leave the study at any moment, with no type of penalisation or loss of benefits to which they were entitled.

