### Criteria and procedures for withdrawal from the study

A patient may be withdrawn from the study at any time, either at will or by decision of the researcher. The reasons for interrupting participation in the study will be recorded on the summary page of the Digital Data Record (DDR). The following procedure is to be followed when a patient withdraws from the study:

• Assess the relevant study variables

• Record any adverse events

• Evaluate the taking of rescue medication

• Indicate the possible co-interventions carried out

• Complete the DDR, record the date and reason for withdrawal.

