### Rescue medication

The patients are allowed to take analgesics and/or NSAIDs if they wish. If they do, this fact, and the daily dose taken, should be recorded in the digital data record (DDR).

• Anti-inflammatory medication

• If taken, the maximum dose allowed is 1 diclophenac pill (50 mg) three times a day for a maximum of 4 weeks.

• Administration instructions: to be taken with meals, to alleviate possible gastric irritation.

• Gastroprotective medication

• Specific indications:

• No past record of ulcers or risk factors such as anticoagulant therapy, association with corticoids, age > 60 years or severe baseline illness (kidney insufficiency, cirrhosis, COPD): NO GASTROPROTECTION

• No past record of ulcers and risk factors such as anticoagulant therapy, association with corticoids, age > 60 years or severe baseline illness (kidney insufficiency, cirrhosis, COPD): GASTROPROTECTION with 200 μg misoprostol every 6 or 12 hours or 20 mg famitidine every 12 hours.

• Past record of ulcers: GASTROPROTECTION with 20 mg omeprazole every 24 hours.

• Contraindications: diclophenac should not be taken by patients allergic to it, to acetylsalicylic acid or other NSAIDs, by patients with a history of asthma, angiodema or rhinitis provoked by NSAIDs, by patients affected by porphyria or with a history of ulcers, coagulation pathologies or haemorrhages. Caution is advised for patients with kidney insufficiency, cardiac insufficiency, hypertension or liver insufficiency.

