### Secondary variables

After the first week of treatment, the level of confidence in the treatment is measured on a Treatment Credibility Scale (TCS) [23]. This was first proposed by Borkovec and Nau [24] and comprised four items that are assessed on a continuous VAS from 0 to 10 (0 totally disagree; 10 totally agree). The following elements are included, but at the baseline interview, only the first two questions are asked:

1. Are you confident this treatment will alleviate the pain you feel?

2. Does the treatment seem a logical one?

3. Would you recommend this treatment to a friend or relative who had the same problem?

4. Do you think this treatment could be applied to other problems?

After three weeks of treatment (T-1) (15 sessions of physiotherapy), the following secondary variables will be assessed by an independent evaluator:

• Pain intensity in the shoulder during the day, on a 10 cm VAS (DPI-VAS)

• Pain intensity in the shoulder during the night, on a 10 cm VAS (NPI-VAS)

• Degree of improvement perceived by the patient (IPP) (7 point Likert categoric scale: 0 much worse; 1 worse; 2 slightly worse; 3 no change; 4 slightly better; 5 better; 6 much better) [25]

• Degree of improvement perceived by the evaluator (IPE) (7 point Likert categoric scale: 0 much worse; 1 worse; 2 slightly worse; 3 no change; 4 slightly better; 5 better; 6 much better)

• NSAIDs taken (NT)

• Treatment Credibility Scale items 3 and 4

• Adverse events (ADEV) of a traumatic nature that might distort the results of the evaluation.

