#### Follow up at 3 months after completing the treatment (T-2)

An independent evaluator and rehabilitation specialist will make the following assessments at 3 months after the treatment ends:

• Score on Constant's Shoulder Function Assessment (SFA) Scale

• Pain intensity in the shoulder during the day, on a VAS (DPI-VAS)

• Pain intensity in the shoulder during the night, on a VAS (NPI-VAS)

• Degree of improvement perceived by the patient (IPP)

• Degree of improvement perceived by the evaluator (IPE)

• NSAIDs taken (NT)

• Adverse events (ADEV)

• Subsequent episodes of shoulder pain, their duration and treatment applied.

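### The end-of-treatment adverse-event item covers only traumatic events that could disturb the shoulder assessment, which is narrower than the rule at withdrawal and misses harms the protocol itself names

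*Protocol article*

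**What the plan says.** Adverse events appear in five places in the Protocol article.

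- **Secondary variables (T-1).** The list opens with "After three weeks of treatment (T-1) (15 sessions of physiotherapy), the following secondary variables will be assessed by an independent evaluator" and ends with "Adverse events (ADEV) of a traumatic nature that might distort the results of the evaluation". This is the only description of the ADEV variable in the article.
- **Follow-up at 3, 6 and 12 months (T-2, T-3, T-4).** Each list names adverse events under the same ADEV label, with no qualifier.
- **Criteria and procedures for withdrawal.** For a patient who leaves the study, the instruction is "Record any adverse events".

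Two further sections name harms. Under Study subjects, patients are told of the "possible risks (infection, lipothymia, hematomas". Under Rescue medication, gastric irritation is recognised as a possible effect of the permitted NSAID, but what is to be recorded is whether medication was taken and the daily dose.

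**The concern.** The T-1 item sets two conditions: the event must be traumatic, and it must be capable of disturbing the evaluation. Together they make the item a nuisance flag for the shoulder score. It is nevertheless labelled as the adverse-event variable, and T-1 is the only scheduled visit that closes the treatment period.

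The active treatment is a needle inserted deep into the lower leg, away from the joint being scored, so its expected harms are the ones least likely to satisfy both conditions. If sites follow the wording, a completer's faint or needle-site infection has no place in the T-1 record, while the same event in a patient who withdraws does. What is at stake is the completeness and consistency of the harm data, not the primary efficacy result.

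**Working it through.** The protocol gives no figure for this point, so the check sets the sections side by side.

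**Step 1. Test each named harm against the T-1 wording.**

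| Harm named in the protocol | Traumatic? | Could distort the shoulder evaluation? | Recorded at T-1 as worded? |
|---|---|---|---|
| Infection (Study subjects) | No | Not ordinarily | No |
| Lipothymia (Study subjects) | No | Not ordinarily | No |
| Leg haematoma (Study subjects) | Arguable | Not ordinarily | Only if it affects the assessment |
| Gastric irritation from the NSAID (Rescue medication) | No | No | No |

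**Step 2. Compare the rule by patient and time.**

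| Situation | Rule |
|---|---|
| Withdrawal | Any adverse event |
| Completer at T-1 | Traumatic and might distort the evaluation |
| T-2, T-3, T-4 | ADEV, no qualifier |

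**Step 3. Does the restriction carry over to T-2 to T-4?** The follow-up lists reuse labels without repeating their detail: the 7-point scale for perceived improvement and the 10 cm length of the VAS are also left out there. That favours carry-over. The plain wording at those visits favours no restriction. The document does not settle it. Even if the later entries are unrestricted, T-2 is three months after treatment ends and T-3 and T-4 are telephone interviews, so short-lived treatment-period events would depend on long recall.

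**Step 4. When would a comparison between arms be distorted?** Let h be the true proportion of patients with an event in an arm, w the share of those patients who withdraw, and s the share of such events that the T-1 wording picks up in completers. The proportion recorded up to T-1 is

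h × [w + (1 − w) × s].

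The ratio of recorded proportions, experimental (E) to control (C), is

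(h_E / h_C) × [w_E + (1 − w_E) × s] / [w_C + (1 − w_C) × s].

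If w_E = w_C, and s is the same in both arms, the second factor is 1 and the ratio is undistorted, although both proportions are too low whenever s < 1 and w < 1. If withdrawal differs by arm, the factor moves away from 1. For events the wording excludes altogether (s = 0), it becomes w_E / w_C.

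**Step 5. Who falls under which rule?** Sample size and associated power gives 188 + 199 = 387 patients required and 226 + 239 = 465 to be enrolled, an allowance of 465 − 387 = 78. On that planning assumption, about 387 patients would come under the T-1 wording and up to 78 under the withdrawal rule. This is an upper figure for the second group, because a patient simply lost to follow-up may have no withdrawal assessment.

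**The case against.** The strongest reply is that the T-1 item is not a safety-reporting rule at all. It sits in a list completed by an evaluator who must not know the treatment, and it may be meant only to flag events that spoil the shoulder score. The article declares compliance with Good Clinical Practice and provides for audits, and a condensed article may leave the safety procedure to a fuller document. Four of the five mentions of adverse events carry no restriction.

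Much of this stands. A missing safety procedure is not a finding here, and three stronger readings should be resisted:

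- A reader might infer that harms are excluded throughout the trial. The text does not say so: withdrawal covers any event and the follow-up entries are unqualified.
- A reader might take "the choice of a simple, safe method to treat this shoulder complaint" as an announced safety conclusion. It appears among the considerations for the discussion and reads as a reason for choosing the method. It does not commit the authors to a safety claim from these data.
- A reader might infer that the comparison of harms is biased. No such comparison is described in Data analysis, the abstract's list of secondary variables has no adverse-event outcome, and the differing rules apply equally in both arms.

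What the reply does not remove is the wording itself. The T-1 restriction is stated, it is the only description the ADEV label receives, and it disagrees with the withdrawal rule. A fuller safety procedure elsewhere would have to be reconciled with it.

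The reply also raises a fair practical point: if the evaluator asks about every adverse event, a patient may mention a faint during needling or a bruise on the leg and so reveal the allocation. Any remedy has to deal with that.

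**Conclusion.** The point holds for completers at T-1. As worded, the adverse-event variable does not cover infection, lipothymia, a leg haematoma that leaves the shoulder assessment unaffected, or gastric effects of the rescue NSAID. It conflicts with the withdrawal rule, and its relation to T-2 to T-4 is unclear.

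The consequence is unequal ascertainment between completers and withdrawers. A contrast between arms would be distorted only if withdrawal, in particular among patients with events, differs by arm; the document gives no reason to expect this and none to rule it out. The number of events missed cannot be estimated, because no event rates are given. A reader might go further and conclude that the trial would report almost no harms; the unrestricted entries elsewhere do not support that.

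The conclusion assumes that sites apply the T-1 wording literally and that no separate record by the treating doctor exists. The efficacy analysis is unaffected. The change is worth making because it is cheap and recruitment is described as still open.

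**What to change.** Reconcile the sections on withdrawal, secondary variables and follow-up with one definition, any adverse event, applied in both arms, at withdrawal and at every visit from T-1. State that it covers the disclosed risks (infection, lipothymia, haematoma) and reactions to rescue medication.

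Keep the traumatic event that might distort the evaluation as a separate flag, for use in a sensitivity analysis of the shoulder score.

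Have the treating doctor record all treatment-revealing events, lipothymia as well as needle-site events, under the doctor's own access code, with the same questions put to patients in the TENS-placebo arm. The device already separates the evaluator's access from the doctor's, so the evaluator can stay blind.

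The cost is a few data fields and slightly longer data entry. Patients already recorded under the narrower wording must be reported separately, because their T-1 records are not comparable with later ones.

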#### Follow up at 3 months after completing the treatment (T-2)

An independent evaluator and rehabilitation specialist will make the following assessments at 3 months after the treatment ends:

• Score on Constant's Shoulder Function Assessment (SFA) Scale

• Pain intensity in the shoulder during the day, on a VAS (DPI-VAS)

• Pain intensity in the shoulder during the night, on a VAS (NPI-VAS)

• Degree of improvement perceived by the patient (IPP)

• Degree of improvement perceived by the evaluator (IPE)

• NSAIDs taken (NT)

• Adverse events (ADEV)

• Subsequent episodes of shoulder pain, their duration and treatment applied.

#### Follow up at 6 months after completing the treatment, carried out by telephone interview (T-3)

An independent evaluator will make the following assessments by telephone interview at 6 months after the treatment ends:

• Score on Constant's Shoulder Function Assessment (SFA) Scale (only the subjective parameters)

• Pain intensity in the shoulder during the day, on a VAS (DPI-VAS)

• Pain intensity in the shoulder during the night, on a VAS (NPI-VAS)

• Degree of improvement perceived by the patient (IPP)

• NSAIDs taken (NT)

• Adverse events (ADEV)

• Subsequent episodes of shoulder pain, their duration and treatment applied.

#### Follow up at 12 months after completing the treatment, carried out by telephone interview (T-4)

An independent evaluator will make the following assessments by telephone interview at 12 months after the treatment ends:

• Score on Constant's Shoulder Function Assessment (SFA) Scale (only the subjective parameters)

• Pain intensity in the shoulder during the day, on a VAS (DPI-VAS)

• Pain intensity in the shoulder during the night, on a VAS (NPI-VAS)

• Degree of improvement perceived by the patient (IPP)

• NSAIDs taken (NT)

• Adverse events (ADEV)

• Subsequent episodes of shoulder pain, their duration and treatment applied.

### Data collection and analysis

Data collection and recording will be carried out using an Dell Axim × 30 PDA, fitted with the Windows^® ^operating system, and specially designed for the purposes of this study, with obligatory fields, validation rules and quality control for error avoidance; a 512 bit encoding system is incorporated to ensure the confidentiality of all the records. Furthermore, as additional functions, it will include a security analysis system with stored passwords, and functions for the export/import and synchronisation of the database content. Access to this PDA will be limited to THREE users: 1) the healthcare centre evaluator; 2) the doctor applying the treatments; 3) the study controller. Each will have a different access code.

The data tables describing the characteristics of the study subjects and the results of each of the evaluations will be entered separately. Each record corresponding to an evaluation, after approval by the researcher responsible, will be stored such that further editing cannot be performed. A backup copy of the database will be encrypted in a 512 bit system and uploaded weekly by safe transmission system to a web server. The study controller will store on the central computer the data obtained from each of the participating healthcare centres and will include all the records in the central database. Similarly, the study controller will make a weekly printout of the updated tables from each of the healthcare centres; these documents will be stored securely and kept as an original record for purposes of inspection or auditing or in case of loss of digital data. Each PDA will be the responsibility of the corresponding researcher at each health centre.

### Sample size and associated power

The sample size was predetermined for a level of significance of 0.05, a power of 0.80 and a final average score on Constant's SFA scale of 70 among the experimental group (standard deviation 17) and 65 among the control group (standard deviation 18), with a two-tailed test, according to data taken from Kleinhenz [17]and Sun [18]. Thus, 188 patients are required for the experimental group and 199 for the control group. Assuming a 20% dropout rate, the final sample size was set at 226 patients for the experimental group and 239 for the control group [26].

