**Methods/design:**

Randomised controlled multicentre study with blind evaluation by an independent observer and blind, independent analysis. A study will be made of 465 patients referred to the rehabilitation services at participating healthcare centres, belonging to the regional public health systems of Andalusia and Murcia, these patients presenting symptoms of painful shoulder and a diagnosis of subacromial syndrome (rotator cuff tendinitis and subacromial bursitis). The patients will be randomised into two groups: 1) experimental (acupuncture + physiotherapy); 2) control (TENS-placebo + physiotherapy); the administration of rescue medication will also be allowed. The treatment period will have a duration of three weeks. The main result variable will be the change produced on Constant's Shoulder Function Assessment (SFA) Scale; as secondary variables, we will record the changes in diurnal pain intensity on a visual analogue scale (VAS), nocturnal pain intensity on the VAS, doses of non-steroid anti-inflammatory drugs (NSAIDs) taken during the study period, credibility scale for the treatment, degree of improvement perceived by the patient and degree of improvement perceived by the evaluator. A follow up examination will be made at 3, 6 and 12 months after the study period has ended. Two types of population will be considered for analysis: per protocol and per intention to treat.

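### The 20% dropout allowance was applied as a 1.2 multiplier, so 465 patients cover about 16.8% dropout at 80% power, not 20%

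*Protocol article*

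**What the plan says.** The protocol article, under *Sample size and associated power*, states its design inputs: "The sample size was predetermined for a level of significance of 0.05, a power of 0.80". The test is two-sided. The assumed final Constant scores are a mean of 70 (SD 17) in the acupuncture arm and a mean of 65 (SD 18) in the placebo arm. From these it concludes that "188 patients are required for the experimental group and 199 for the control group", which is 387 in total. The dropout step follows: "Assuming a 20% dropout rate, the final sample size was set at 226 patients for the experimental group and 239 for the control group". The abstract, under *Methods/design*, repeats the resulting total: "A study will be made of 465 patients". No other dropout rate appears in the article, and no reason is given for the factor used.

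**The concern.** The final numbers look like the required numbers plus 20%, which is not the same as allowing for the loss of 20% of those enrolled. If a fraction d of the patients drops out, N enrolled leave N(1 − d), so keeping n requires N = n/(1 − d). Multiplying by (1 + d) always falls short, because (1 + d)(1 − d) = 1 − d². With d = 0.20 that product is 0.96, so about 4% of the required patients are missing even when dropout is exactly as planned.

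What is at stake is whether the sample-size statement is true. A reader will take it that the trial keeps 80% power when one patient in five is lost. The plan's own inputs do not support that.

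**Working it through.** **Inputs**, all from *Sample size and associated power*: two-sided α = 0.05; power 0.80; means 70 and 65 (difference 5); SDs 17 and 18; required 188 and 199; dropout 20%; final 226 and 239.

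**1. Reproduce the required numbers.** The ratio 188:199 is close to 17:18, so the arms appear to have been allocated in proportion to the SDs. With (z₀.₉₇₅ + z₀.₈₀)² = 7.849:

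- Experimental: 7.849 × 17 × (17 + 18) / 5² = 186.8
- Control: 7.849 × 18 × (17 + 18) / 5² = 197.8

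These round up to 187 and 198, one below the stated figure in each arm. Power at 188/199 is 0.802 by the normal approximation and 0.8005 by the unequal-variance t-test. The base calculation is sound and has almost no slack.

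**2. Reproduce the final numbers.**

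- 188 × 1.2 = 225.6, rounded up to 226
- 199 × 1.2 = 238.8, rounded up to 239

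Both stated figures match exactly.

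**3. Apply the 20% as a dropout rate.**

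- 188 / 0.8 = 235
- 199 / 0.8 = 248.75, rounded up to 249
- Total 484, against 465 stated: a difference of 19

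**4. What 465 leaves after 20% dropout.**

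- 226 × 0.8 = 180.8, about 181
- 239 × 0.8 = 191.2, about 191
- Total 372, which is 387 − 372 = 15 below the requirement

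**5. Power at 181/191.** The standard error of the difference is √(17²/181 + 18²/191) = √(1.597 + 1.696) = 1.815. Then 5 / 1.815 = 2.755, and Φ(2.755 − 1.960) = 0.787. The t-test version gives 0.785. The difference detectable at 80% power is (1.960 + 0.842) × 1.815 = 5.08 points, against the planned 5.

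**6. Dropout that 465 does cover.** 1 − 387/465 = 16.8% overall (16.8% in the experimental arm, 16.7% in the control arm).

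Power of the 226/239 design at other dropout rates (normal approximation, unadjusted final scores):

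| Dropout | Patients left | Power |
|---|---|---|
| 0% | 465 | 0.869 |
| 10% | 418.5 | 0.832 |
| 15% | 395.25 | 0.811 |
| 20% | 372 | 0.787 |
| 25% | 348.75 | 0.760 |

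**The case against.** There are four arguments for leaving the figure alone.

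- **The effect is very small.** Power falls by about 1.5 points and the detectable difference rises by 0.08 on a 100-point scale. The means and SDs come from two earlier studies, one of which the *Background* describes as having 13 and 22 patients. Uncertainty in those inputs probably outweighs this error. This stands, and it limits the weight of the point.
- **The 78.5% is not the power of the planned primary analysis.** *Data analysis* adjusts the change in SFA score for baseline. With the usual variance factor (1 − r²), 372 patients do the work of 387 once r² = 1 − 372/387 = 0.039, that is, r of about 0.20. At r = 0 the shortfall remains; at r of about 0.2 or more it is gone. This also stands as a possible offset. However, the article states no correlation, and its sample size is built on unadjusted final scores.
- **Not every dropout is lost to the primary endpoint.** *Population* makes all randomised patients the main analysis set, the withdrawal procedure asks for study variables to be assessed on leaving, and the primary endpoint falls at three weeks while follow-up runs to twelve months. The article does not say to which period the 20% applies, so more than 372 may contribute. Even so, the sample-size section itself enlarges the trial for dropout, which treats dropouts as not counting towards the 387. If they did count in full, no inflation would be needed. On neither reading does 465 follow from 387 and 20%.
- **The 20% may have been meant as a mark-up.** The text calls it a dropout rate. If a mark-up was intended, the wording is wrong and needs the same correction.

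**Conclusion.** The concern holds. The required 387 is right; the dropout step is wrong, and 465 patients, 20% dropout and power 0.80 cannot all be true under the stated inputs. At 20% dropout, power is 78.5% (t-test) or 78.7% (normal approximation). Power of 80% is kept up to about 16.8% dropout. These figures assume an unadjusted comparison of final scores, the stated means and SDs, equal dropout rates in the two arms, and no primary outcome from patients who drop out. The practical effect is minor, it does not call the design into question, and a modest baseline correlation would remove it. It is an error in a stated figure, and it should be put right where it stands.

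**What to change.** Keep 465 and correct the sentence in *Sample size and associated power* in one of two ways:

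- state that 226 + 239 = 465 allows for about 16.8% dropout at 80% power; or
- state that 465 with 20% dropout leaves 372 patients and about 78.5% power for the unadjusted comparison of final scores.

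The sponsor may add that baseline adjustment is expected to recover the loss, provided the assumed correlation between baseline and final score is given. The figure of 484 shows what a true 20% allowance would have been; it is not a request for 19 more patients. The cost is one sentence and a slightly less favourable stated figure. The total in the abstract can stay as it is.
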